### Intervention

#### Dietary intervention

All women will receive standard GDM dietary advice in line with evidence-based guidelines [2, 40, 43, 44]. Women will be encouraged to consume a minimum carbohydrate intake of 175 g per day, from mostly low glycaemic sources, distributed across the day over three meals and three snacks. The dietary advice will promote a low saturated fat intake and higher consumption of vegetables, fruit, dairy and whole grains.

After Baseline data are collected, women who are randomised to either of the two dietary intervention groups (RS Diet & RS Supp) will receive additional dietary education on consuming a high RS diet commencing on Day 3. All RS dietary education will be conducted by the PI who is an experienced Accredited Practising Dietitian (APD). A standardised teaching plan (Supplement 3) and education materials will be utilised (Supplements 4 & 5). Participants will be provided with written material including a Gut Feeling cookbook [45] and sample menus, as well as some non-perishable samples of high RS foods to allow for immediate adoption of the diet. Dietary RS will be measured at Baseline, Day 10 and Day 56 using 3-day weighed food records (Supplement 6). Evidence of compliance with the high RS diet will also be monitored via urine samples for metabolomic analysis and change in stool microbiota at the same timepoints. Participants will be asked to continue the high RS diet until the delivery of their child.

The RS education tools and strategies have been piloted in a non-pregnant population and achieved a median increase in dietary RS intake of ≥6.6 g RS per day (unpublished data). The typical intake of RS in Australian women aged 19–44 years has been estimated to range from 2.9–8.3 g per day [46]. Similarly, recent data from the United States estimated the mean daily intake of RS to be 1.9 g per 1000 kcal for women of this age [47], which would equate to 3.8–5.7 g per day.

#### RS supplement

The RS Supp group will consume an RS supplement of high-amylose maize (HAMS) type 2 resistant starch. Participants will be given a 600 g tub of HAMS each fortnight, along with a 40 ml scoop. They will be instructed and provided with written material (Supplement 7) on how to prepare and incorporate the RS supplement into cool fluids or foods in their diet. As with all low-digestible carbohydrates, gastrointestinal (GI) discomfort is a known side effect of rapid introduction of RS, therefore, participants will introduce HAMS over a two-day adjustment period. They will be instructed to consume 1 scoop (20 g) per day for 2 days, taking half in the morning and the rest at night. Then, increasing to a dose of 1 scoop (20 g) morning and night for the remainder of their pregnancy. The RS supplement contains 40% RS type 2. The final amount of RS in the 40 g of HAMS per day will be 16 g, which is below the level of 45 g per day of RS supplementation that is known to be tolerated with minimal side effects, most of which are flatulence [48]. Intakes of up to 80 g RS per day have been tolerated without diarrhoea [48]. Those in the high RS diet plus RS supplement are unlikely to achieve this amount. Consumption and compliance of the RS supplement will be monitored by weight of unconsumed HAMS returned fortnightly. Participants will use a daily RS supplement diary to record intake as an additional measure of compliance. We have shown in a recent 2-week feasibility study, 100% compliance with consumption of the RS supplement and minimal GI side effects in 10 female participants with prediabetes or T2DM (unpublished). GI tolerance of the supplement will be measured via a daily bowel symptom diary for the first 10 days and Days 47 to 56.

Participants can withdraw from the study at any time for any reason. Participants will be withdrawn by the investigator if they commence antibiotics, steroids, metformin or if they can no longer comply with the study’s schedule of assessments (Table 1).

**Table 1 Tab1:** Participant measurements and collection summary

	Day 1	Day 3	Day 10	Day 28	Day 42	Day 56	Day 7 post-partum
Recruitment & consent	√						
Randomisation of subjects	√						
Attend clinic	√	√	√		√	√	
Self-monitoring blood glucose data collection		√	√			√	
FreeStyle Libre Pro application	√				√		
Questionnaires:							
medical Hx	√						
medication	√						
GI symptoms	√		√			√	
Quality of Life SF36	√		√			√	
Weight measured	√		√			√	
3-day weighed food records collected		√	√			√	
Bowel symptoms, RS supplement, medication & exercise diary collected		√	√			√	
H_2_ breath test		√	√			√	
Fasting Bloods			√			√	
Maternal stool samples		√	√			√	√
Neonatal stool sample							√
Maternal urine sample		√	√			√	
Neonatal urine sample							√
Breastmilk sample							√
Study instructions and materials							
RS diet education		√					
supplement regime if applicable		√					
Reminder phone call or text				√			
Assessment of Medical Records for							√
adverse outcomes							
delivery method							
birth weight, length							
feeding method							
NICU admission							
length of stay							

*Note: RS* Resistant starch, *NICU* Neonatal Intensive Care Unit

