### Recruitment

Women with newly diagnosed GDM who are potentially eligible to participate in the study will be given a study flyer. When attending clinic for standard GDM education, the Principal Investigator (PI) will explain the study and screen for eligibility, then invite eligible women to participate and provide written consent. The Participant Information Letter is provided in Supplement 1 and Participant Consent form in Supplement 2. Consent for data to be collected on the neonate will also be obtained.

Participant retention will be supported through undertaking study requirements at routine antenatal visits, complimentary parking, text reminders, supportive telephone contact from the PI between widely spaced appointments, and regular contact with the obstetric and midwifery team. Participants who withdraw consent to provide stool and urine samples will be given the option of providing fasting glucose samples.

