### Primary outcome

#### Fasting blood glucose

The primary outcome of this study will be a reduction in median FBG from Baseline, within and between groups. Baseline FBG will be recorded from the diagnostic OGTT results [41]. Subsequent venous blood samples will be collected after an overnight fast at Day 10 and Day 56 and analysed for FBG following protocols from the National Association of Testing Laboratories. FBG within treatment targets (< 5.1 mmol/L) [49] is the measure of glycaemic control that has been most difficult to achieve with standard GDM diet and lifestyle interventions and therefore the variable most likely to indicate the need for medical therapy, such as insulin [50]. If FBGL below 5.1 mmol/L is not achieved by Day 10, insulin therapy will commence. Participants treated with insulin will remain in the study.

Routinely women will receive self-monitoring of blood glucose (SMBG) education. Participants will be provided with an SMBG meter and instructed on measuring blood glucose levels four times daily (FBG and 2-h post-prandially). The SMBG meters used will be either Contour Next (Ascensia Diabetes Care, Switzerland), Accu-Chek Guide (Roche Diabetes Care, Switzerland) or One Touch Verio (LifeScan, USA) and meet International Organization for Standardization (ISO) standards for accuracy. Data from these models will be uploaded via the Diasend Uploader (Glooko, USA). FBG will be monitored on the first 2 days and averaged to provide a Baseline measure. This will be compared to the moving averages over the subsequent 8 days of testing, and then again between Days 48 and 56, across the three dietary groups (Control, RS Diet and RS Supp) using mixed model ANOVA with group-by-time interaction.

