#### Requirement for insulin treatment

Data from the participants’ DMR will determine the percentage of women requiring insulin to control blood glucose levels at Day 10 and Day 56 compared to the control group. Participants who require insulin will remain in the study and all samples will be collected. The commencement of insulin to manage glycaemia requires more health care monitoring and intervention, adding burden to the woman and the health care system [18].

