### Data management

Individually identifiable data will be coded as soon as possible. Data and codes will be kept in separate lockable filing cabinets within a swipe card accessible office and access to the data will be restricted to the research team. Electronic data will be kept in a de-identified format and stored on a password-protected computer or secure server and for a minimum of 25 years. At the end of the retention period, data files and any hard copy source data will be deleted/shredded as per the South Metropolitan Health Service and Edith Cowan University data management requirements. Data collected on participants who later withdraw will be used in analysis if required unless consent to use it has been withdrawn.

The trial investigators/institutions will permit trial-related monitoring, audits, and regulatory inspections, providing direct access to source data/documents. This may include, but not limited to, review by Human Research Ethics Committees and institutional governance review bodies.

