### Statistical analyses

Baseline demographic and outcome variables will be described and compared for differences between groups. Continuous variables will be described as mean ± standard deviation (SD) and nominal and ordinal variables as frequencies and proportions. All continuous variables will be examined for normality using the Shapiro-Wilk test. Descriptive statistics for non-normal continuous variables will be presented as median ± interquartile range (IQR).

FBG and PPBG will be monitored on the first 2 days and averaged to provide a Baseline measure of each outcome. These will be compared to those measured over the subsequent 8 days, and then again between Days 48 and 56, across the three dietary groups (Control, RS Diet and RS Supp) using linear mixed modelling with group-by-time interaction. Analysis will assess if a 0.3 mmol/L reduction is achieved. Demographic variables such as age, pre-pregnancy BMI, parity and ethnicity will be adjusted in the model. Statistical analyses will be performed using SPSS® (Statistical Package for Social Sciences, version 27 for Windows).

The number of PPBG excursions experienced by a participant per day between Days 4 to 10 will be examined and compared relative to the number determined at their Baseline over the first 2 days of the usual care diet. Generalised Mixed Modelling will be utilised to assess whether a dietary change reduces the frequency of PPBG excursions as compared with norm with adjustments for relevant demographic variables.

Different R packages and PRIMER 7 (Quest Research, NZ), a non-parametric statistical software package, will be used to assess change within and between groups for microbial composition. Distance Based Linear Modelling (DistLM) will be used to look for a correlation between change in stool microbiota or SCFA & measures of glycaemia.

Direct and indirect costs savings related to any reduction in insulin treatment or improvements in maternal and neonatal outcomes will be calculated from DRG codes, Weighted Activity Units (WAU) and the National Efficient Price (NEP) and reported [74].

Missing data will be treated in statistical analysis as missing and coded as 999 or left blank, so as not to affect the accuracy of the analysis. Prior to any statistical analysis, all data will be explored for outliers. Any outliers found will be cross-checked with the source file. Any true outliers will be checked with the clinician before being removed/left in the dataset.

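### Women who start antibiotics, steroids or metformin are withdrawn with no stated provision for later fasting glucose or birth outcomes, although women who start insulin are kept

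*Protocol article*

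**What the plan says.** The withdrawal rule is in the RS supplement section: "Participants will be withdrawn by the investigator if they commence antibiotics, steroids, metformin", or if they can no longer keep to the assessment schedule. The sentence just before it reads "Participants can withdraw from the study at any time for any reason". No wording limits the rule to stopping the diet or supplement, or to the stool-based endpoints.

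Insulin is handled the other way. The Fasting blood glucose section says "Participants treated with insulin will remain in the study", the section on insulin requirement says "Participants who require insulin will remain in the study and all samples will be collected", and Sample size repeats that these women stay.

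Three further statements bear on what happens to the data:
- Recruitment: "Participants who withdraw consent to provide stool and urine samples will be given the option of providing fasting glucose samples".
- Data management: "Data collected on participants who later withdraw will be used in analysis if required unless consent to use it has been withdrawn".
- Statistical analyses: "Missing data will be treated in statistical analysis as missing and coded as 999 or left blank".

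The primary outcome is defined thus: "The primary outcome of this study will be a reduction in median FBG from Baseline, within and between groups", with venous samples at Day 10 and Day 56. Birth and NICU data come from the digital medical record after discharge.

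**The concern.** A microbiome reason for the rule is easy to see: stool composition after these drugs would be hard to attribute to resistant starch. That reason supports excluding later stool and related samples. It does not explain why a woman's FBG, insulin status, birth weight or NICU admission should stop being followed.

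Starting one of these drugs happens after randomisation and may be related to the outcome. Metformin could be started because glucose is not controlled. Steroids or antibiotics could mark a complicated pregnancy. Both links are assumptions, since the protocol gives no indications for these drugs. Neither participants nor investigators are blinded, so the decision to start a drug could also depend on arm. If follow-up stops at such events, the women left in each arm need not be comparable, and outcomes that occur later in the withdrawn women may not be counted.

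**Working it through.** **1. Does any section keep the data?**

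| Data | Provision after an investigator withdrawal |
|---|---|
| FBG at Day 10 or Day 56, if later than the drug start | None stated. The glucose-only option in Recruitment covers women who themselves decline stool and urine samples. |
| FBG before the drug start | May be used, but only *if required* (Data management) |
| Insulin status at Day 56 | None stated |
| Birth weight, NICU admission, delivery | None stated. Collected after discharge, so always later than an antenatal withdrawal. |

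Missing values are simply treated as missing. No separate handling is given for drug-triggered withdrawal.

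**2. The plan's own scale.** Sample size gives a mean FBG of 5.175, SD 0.86 and target difference 0.3 mmol/L. 0.3 / 0.86 = 0.349, which reproduces the stated d = 0.35.

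**3. Illustration: difference in mean FBG among completers.** The withdrawal proportions (pc in Control, pr in a resistant starch arm) and the excess u of withdrawn women above their arm mean are assumptions; u runs from 0.5 to 0.86 mmol/L (one SD). Removing a proportion p lowers the mean of those left by p·u/(1−p), so the Control-minus-RS difference shrinks by

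pc·u/(1−pc) − pr·u/(1−pr)

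| pc vs pr | u = 0.5 | u = 0.86 |
|---|---|---|
| 10% vs 5% | 0.0556 − 0.0263 = 0.029 | 0.0956 − 0.0453 = 0.050 |
| 20% vs 10% | 0.1250 − 0.0556 = 0.069 | 0.2150 − 0.0956 = 0.119 |

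Against 0.3 mmol/L this is 0.029/0.3 = 10% to 0.119/0.3 = 40% of the target. A second model with no true effect takes FBG as normal (5.175, 0.86). It removes women either at random from those at or above 5.1 mmol/L or strictly from the top. It gives 0.04 to 0.07 and 0.09 to 0.13 for the same two pairs of rates. With equal rates in both arms, the between-group difference is roughly unbiased under no effect, but the within-group change is not. The primary outcome names both.

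**4. What the planned mixed model does.** The model uses Baseline and earlier values of women lost later. A simulation used SD 0.86, assumed correlation 0.5 or 0.7 between visits, a true effect of 0.3, the same two pairs of rates, and withdrawal after Day 10 with probability rising with glucose.

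| Withdrawal driven by | Completers' Day 56 difference | Likelihood estimate of difference in change |
|---|---|---|
| Observed Day 10 glucose | 0.23 to 0.27 | 0.30 (no bias) |
| Unobserved Day 56 glucose | 0.20 to 0.25 | 0.22 to 0.27 (bias about 0.03 to 0.08) |

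The shift in step 3 is therefore what completers alone would show. The mixed model removes it when withdrawal depends on recorded glucose and only part of it otherwise. This holds only if the earlier values are actually used, which *if required* leaves open. Birth outcomes are measured once, so a repeated-measures model has no earlier value to draw on.

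**The case against.** The strongest counter-argument is that the protocol's stated step for uncontrolled fasting glucose is insulin, started if FBG is not below 5.1 mmol/L by Day 10, and insulin starters stay. Metformin appears only as an exclusion criterion and a withdrawal trigger, beside steroids and antibiotics in both places, so the different treatment follows the eligibility criteria. This stands. A reader might infer that the rule removes the dietary failures from the trial, but the documents do not support that. It would remove only those started on metformin, and the protocol does not describe metformin as the next step when diet fails.

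A reader might also infer that complicated pregnancies are systematically removed. The protocol does not say why steroids or antibiotics would be given, and drugs given around delivery would mostly come after Day 56 (about 36 weeks), too late to affect FBG.

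Nor does the text say that birth and NICU data are dropped. It is silent: record collection is not expressly restricted to women still enrolled, and the phrase about leaving the study belongs to the sentence on voluntary withdrawal. This softens the point without answering it. Followed as written, the rule gives no basis for continued collection, and an analysis plan cannot restore samples never taken.

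Finally, the rates are unsupported, and in this illustration the bias runs towards no effect. Both are fair, and both bear on severity.

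**Conclusion.** The concern holds in a limited form. The rule is not confined to the microbiome endpoints, no section provides for primary-outcome or medical-record follow-up after it is applied, and it sits beside the opposite handling of insulin. The comparison may therefore not be as randomised.

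The size and direction of any bias are unknown. The figure of 0.03 to 0.12 mmol/L rests on assumed, unequal withdrawal rates and an assumed excess in withdrawn women, and it applies to a completer comparison. Under the planned mixed model it would largely vanish if withdrawal depends on observed glucose. The exposure that remains is withdrawal driven by unrecorded glucose, and birth outcomes measured once.

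A reader might also infer that ending these withdrawals would restore a stated amount of power. The documents do not support this: they do not say how much of the 30% attrition comes from the rule, and retained women may be off intervention or on altered treatment. The point merits correction (should-fix) and does not invalidate the design.

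**What to change.** - Reconcile the metformin and insulin passages, so that it is clear why one group leaves and the other stays, and what leaving means for data collection.
- Separate exclusion from the microbiome analyses from leaving follow-up. State that Day 10 and Day 56 FBG, medication use and medical-record outcomes continue to be collected for every randomised woman who still consents, and that they are analysed as randomised.
- Exclude or flag only the stool, short-chain fatty acid, breath and breastmilk samples taken after one of these drugs is started.
- In Data management, delete *if required*, so that use of data collected before withdrawal depends only on consent.

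The cost is a minor protocol amendment. Recruitment already places study requirements at routine antenatal visits, and birth data are in the medical record. The downside is that some women with altered treatment or off intervention enter the primary analysis, which may dilute the effect. No prescribing decision changes.

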### Primary outcome

#### Fasting blood glucose

The primary outcome of this study will be a reduction in median FBG from Baseline, within and between groups. Baseline FBG will be recorded from the diagnostic OGTT results [41]. Subsequent venous blood samples will be collected after an overnight fast at Day 10 and Day 56 and analysed for FBG following protocols from the National Association of Testing Laboratories. FBG within treatment targets (< 5.1 mmol/L) [49] is the measure of glycaemic control that has been most difficult to achieve with standard GDM diet and lifestyle interventions and therefore the variable most likely to indicate the need for medical therapy, such as insulin [50]. If FBGL below 5.1 mmol/L is not achieved by Day 10, insulin therapy will commence. Participants treated with insulin will remain in the study.

Routinely women will receive self-monitoring of blood glucose (SMBG) education. Participants will be provided with an SMBG meter and instructed on measuring blood glucose levels four times daily (FBG and 2-h post-prandially). The SMBG meters used will be either Contour Next (Ascensia Diabetes Care, Switzerland), Accu-Chek Guide (Roche Diabetes Care, Switzerland) or One Touch Verio (LifeScan, USA) and meet International Organization for Standardization (ISO) standards for accuracy. Data from these models will be uploaded via the Diasend Uploader (Glooko, USA). FBG will be monitored on the first 2 days and averaged to provide a Baseline measure. This will be compared to the moving averages over the subsequent 8 days of testing, and then again between Days 48 and 56, across the three dietary groups (Control, RS Diet and RS Supp) using mixed model ANOVA with group-by-time interaction.

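### The primary outcome is defined on venous FBG with an OGTT baseline, but the FBG models set out in detail use a 2-day baseline and multi-day self-monitored windows, so two different primary results are possible

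*Protocol article*

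**What the plan says.** Under the Fasting blood glucose heading of Primary outcome, the first paragraph gives one definition:

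- Summary: "The primary outcome of this study will be a reduction in median FBG from Baseline, within and between groups".
- Baseline: "Baseline FBG will be recorded from the diagnostic OGTT results".
- Follow-up: "Subsequent venous blood samples will be collected after an overnight fast at Day 10 and Day 56".

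The second paragraph, under the same heading, turns to self-monitoring meters and gives another:

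- Baseline: "FBG will be monitored on the first 2 days and averaged to provide a Baseline measure".
- Follow-up: "This will be compared to the moving averages over the subsequent 8 days of testing, and then again between Days 48 and 56".
- Model, attached to this series: "using mixed model ANOVA with group-by-time interaction".

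Statistical analyses repeats the second version: "FBG and PPBG will be monitored on the first 2 days and averaged to provide a Baseline measure of each outcome". It uses the same day windows in a linear mixed model with group-by-time interaction, then says the analysis will judge whether a 0.3 mmol/L reduction was reached. It mentions no OGTT value, venous sample, median or moving average.

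Three other places fit the first version. Sample size assumes three time points (Baseline, Day 10, about Day 56). Table 1 ticks fasting bloods at Day 10 and Day 56 only. The abstract lists fasting plasma glucose at Baseline, Day 10 and Day 56.

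**The concern.** The two versions differ in instrument (laboratory venous or capillary meter), baseline (one OGTT value or a 2-day mean), follow-up (single days or multi-day windows) and summary measure (median or modelled mean). The text does not rank them, so a team following it faithfully could produce two primary results that disagree, and could choose between them after seeing the data. Participants and investigators are not blinded, which makes that risk practical.

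The baseline choice also matters for the within-group part of the outcome. Women enter on the OGTT, and a fasting value of 5.1 mmol/L or more is one of the qualifying criteria. A fall from that value partly reflects regression to the mean, so the two baselines need not give the same within-group change.

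A further question arises for the self-monitored series. Adjacent moving averages share readings, so they are not separate observations. The window length and the covariance structure are not stated.

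**Working it through.** **1. The two versions side by side**

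| Item | Primary outcome, first paragraph | Primary outcome, second paragraph, and Statistical analyses |
|---|---|---|
| Source | Venous sample | Meter (named in the second paragraph; inferred from the day windows in Statistical analyses) |
| Baseline | Diagnostic OGTT | Mean of first 2 days |
| Follow-up | Day 10, Day 56 | Days 3-10, Days 48-56 |
| Summary | Median | Mean, by mixed model |
| Matches Sample size, Table 1, abstract | Yes | No |
| Carries the 0.3 mmol/L target in Statistical analyses | No | Yes |

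Venous sampling on two days cannot supply a 2-day mean or an 8-day series. The glucose sensor could in principle, but its funding is not secured and neither model paragraph mentions it.

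Day 3 is also handled inconsistently. It is baseline in Overview of study design and in Post-prandial glucose (both Days 1-3). It is follow-up here, because the 8 days after the first 2 are Days 3-10. It is in neither period in the analysis of post-prandial excursions (first 2 days against Days 4-10).

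**2. Which version the sample size belongs to**

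Stated inputs: difference 0.3 mmol/L, SD 0.86, k = 3 groups, m = 3 time points, f = 0.175, 80% power, alpha 5%. Assumed, because it is not stated: correlation between time points rho = 0.5, with sphericity.

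- d = 0.3 / 0.86 = 0.349; f = d / 2 = 0.174.
- Noncentrality = N f² m / (1 − rho) = 69 × 0.175² × 3 / 0.5 = 12.7.
- df = (k − 1)(m − 1) = 4 and (N − k)(m − 1) = 132.
- Power at N = 69 is 81.1%. The smallest N is 68, or 69 as a multiple of 3.

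The stated 69 is reproduced as a three-time-point group-by-time interaction. Moving averages would give a different layout: a 2-day window yields 1 baseline + 7 + 8 = 16 points, and a 7-day window 1 + 2 + 3 = 6.

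**3. Success on either source**

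Two independent 5% tests: 1 − 0.95² = 9.75%. The sources are correlated, so this was also simulated under no effect: 23 women per group, three time points, between-woman SD 0.6, measurement SD 0.3 (venous) and 0.4 (meter), 6,000 runs. All SDs are assumptions.

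| Shared woman-by-period SD | Either test significant | Tests disagree |
|---|---|---|
| 0 | 10.1% | 9.9% |
| 0.2 | 9.1% | 8.7% |
| 0.3 | 9.5% | 8.8% |
| 0.5 | 8.7% | 7.4% |

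**4. Moving averages in a group-by-time ANOVA**

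No effect, 23 per group, between-woman SD 0.6, day-to-day SD 0.6, woman-by-period SD 0, 0.2 or 0.3 (all assumed), 2,000 runs each. Type I error at nominal 5%, as ranges over the three woman-by-period SDs:

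| Window | Sphericity assumed, uncorrected | Greenhouse-Geisser corrected |
|---|---|---|
| 2 days | 7.0-10.7% | 3.5-4.6% |
| 3 days | 9.9-13.1% | 4.1-5.6% |
| 5 days | 11.6-14.5% | 3.9-5.2% |
| 7 days | 11.0-11.7% | 4.6-5.5% |

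Daily readings without averaging gave 4.6-6.0%. One mean per window gave 4.8-7.0% uncorrected and 4.2-5.8% corrected. Monte Carlo standard error is about 0.5 to 0.8 points.

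**The case against.** The best defence is that this is a drafting overlap. The abstract, Sample size, Table 1 and the opening of Primary outcome all point to venous FBG, and the meter paragraph is introduced as routine care. That stands as a reason to choose venous FBG. It does not settle the text, because Statistical analyses ties the 0.3 mmol/L target to the 2-day-baseline series and never mentions the venous one.

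Several stronger readings are tempting, and the document does not support them:

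- *The self-monitored analysis has inflated error.* The article fixes neither window length nor covariance structure, and Statistical analyses names a linear mixed model without moving averages. Covariance structure is commonly left to a SAP. The inflation is conditional: it disappears when non-sphericity is corrected.
- *Two sources, two times and two arm contrasts make eight tests, so the risk is 1 − 0.95⁸ = 34%.* The plan specifies one group-by-time interaction over three groups, not eight pairwise tests. Such tests would also share women, a Control arm and baselines, so they could not be independent.
- *No model exists for venous FBG.* The abstract and Sample size imply a three-point repeated-measures analysis of it, though without detail.
- *The first window creates false positives by including the start of the diet and supplement.* It would more likely dilute an effect. What remains is that Day 3 is assigned inconsistently.

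The order in which the RS arms are compared with Control is a separate matter that a SAP may settle, and it is no part of this point.

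**Conclusion.** The point holds as a contradiction in the text, not as missing detail. Source, baseline, follow-up and summary measure of the primary outcome differ between its definition and the models described in detail, and nothing reconciles them.

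Taking success on either source costs a false-positive risk of up to about 10% instead of 5%. The bound of 9.75% needs only two 5% tests and independence; the simulated 8.7-10.1% rests on assumed variances.

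The possible further inflation to about 7-15% applies only if overlapping moving averages of 2 to 7 days are analysed with sphericity assumed and uncorrected, again under assumed variances.

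The stated 69 is not in question here. It is reproduced for the three-point design at an assumed rho of 0.5, which itself indicates that the three-point venous series is the outcome the trial was sized on.

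**What to change.** In Primary outcome and Statistical analyses:

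1. Name laboratory venous FBG as the single primary variable, with the OGTT fasting value as baseline and follow-up at Day 10 and Day 56.
2. Analyse it as a between-group difference in means, in the linear mixed model with group-by-time interaction on which the sample size rests. Attach the 0.3 mmol/L target to this analysis.
3. Delete the word median from the definition.
4. Make self-monitored FBG secondary. Replace the moving averages by daily readings with serial correlation modelled, or by one mean per window.
5. Make the baseline days for self-monitored FBG agree with Overview of study design and Post-prandial glucose, so that Day 3 is on one side only.

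The cost is an edit to the protocol wording, dated before any outcome data are examined. Every measurement is already scheduled, and neither 69 nor 90 changes.
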